## **6.6 Follow-up of subjects withdrawn from treatment**

No follow-up will take place after subjects have been withdrawn from the study.

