### Clinical tests

All clinical tests and questionnaires measuring walking impairments, mobility, activities of daily life, falling and quality of life are performed according to the specific test protocols. During the first 18 weeks of the study most clinical tests will be repeated with 2-week intervals. Furthermore, the tests will be repeated 6 and 12 months after stroke (T26 and T52, respectively). All the clinical tests are performed with AFO.

The frequency of performing the various measurements is listed in Table 1.

Spasticity of the lower limb is assessed using the Mappam procedure. The subject is in a comfortable semi-reclined position (45°) with support for the back and lumbar region. Knee flexor and extensor muscles are recorded while performing the pendulum test (passive swing movement of the lower leg from full extension and then released), and during passive movement. The subject is instructed to relax his/her leg and not to oppose or facilitate the passive movements. The subject is asked to perform an active movement. The knee joint angle is measured with an electric goniometer placed on the lateral side of the knee. Surface EMG records the activity of the m. Rectus femoris and the Semitendinosus muscles. Electrode placement, skin preparation and related issues are performed according to the guidelines presented by SENIAM (Hermens et al. 1999).

Table 1: Measurements to be performed

| Period                               | Measurement                                                                                                                                                                                                                                                    | Content                                                                                                                                                                                |                                               |
|--------------------------------------|----------------------------------------------------------------------------------------------------------------------------------------------------------------------------------------------------------------------------------------------------------------|----------------------------------------------------------------------------------------------------------------------------------------------------------------------------------------|-----------------------------------------------|

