## **6.4 Withdrawal of individual subjects**

Subjects can leave the study at any time for any reason if they wish to do so without any consequences. The investigator can decide to withdraw a subject from the study for urgent medical reasons.

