### **6.4.1 Specific criteria for withdrawal**

Subjects will be withdrawn when either the subject him/herself or the researcher indicates that the load of the measurements is too much.

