## **6.5 Replacement of individual subjects after withdrawal**

Individuals withdrawn from the study will be replaced by new subjects using “modified intention to treat analysis” in case individuals are withdrawn before start of the intervention (using an AFO).

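### Excessive measurement load leads to full study withdrawal with no follow-up, so low-burden main endpoints are lost even from subjects willing to give them

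*Protocol*

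**What the plan says.** Section 6.4 deals with leaving the study: subjects may do so whenever they wish, and "The investigator can decide to withdraw a subject from the study for urgent medical reasons". Under it, 6.4.1 adds a further ground: "Subjects will be withdrawn when either the subject him/herself or the researcher indicates that the load of the measurements is too much". The wording is not optional, and no lighter schedule is mentioned as a first step.

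The heading of 6.6 is "Follow-up of subjects withdrawn from treatment", but its single sentence concerns the study: "No follow-up will take place after subjects have been withdrawn from the study". Section 6.5 provides replacement only "in case individuals are withdrawn before start of the intervention", so later withdrawals are neither replaced nor followed.

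Table 1 in 6.3 marks the Barthel Index, Rivermead Mobility Index (RMI) and Nottingham Extended ADL (NEADL) as questionnaires and the Functional Ambulation Categories (FAC) as a rating scale. All four are main endpoints in 6.1.1. The NEADL is scheduled only at T26 and T52. The remaining main endpoints (10-metre and 6-minute walks, Timed Up and Go, stair test, Berg Balance Scale) are marked as physical tests, as are gait analysis and the Mappam procedure.

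**The concern.** The two sections together tie a problem with the measurements to the loss of every later measurement. Two things are at stake.

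- **Avoidable missing data.** A subject for whom the gait laboratory or the stair test is too much may still be able and willing to give four of the main endpoints. The plan does not ask. An SAP can model what is missing, but it cannot supply observations that the protocol chose not to collect.
- **Risk to the comparison.** Much of the load is walking, stair climbing and balance, which is what the main endpoints measure. Weaker walkers are the likeliest to reach the limit. Until T9 the late group practises without an AFO, while the early group has one. Section 6.2 states that blinding is not possible, so a researcher who may trigger withdrawal can know the arm. Unequal loss is therefore plausible, though nothing in the protocol shows that it will occur.

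**Working it through.** **The rules side by side.** Ground for withdrawal: measurement load (6.4.1). Scope: the study (6.4, and the text of 6.6). Consequence: no further data (6.6). Relief offered: rest breaks and tests spread over the week (Summary, 9.3), but no option to drop some tests and keep others. Two-weekly testing from T1 to T18 gives nine sessions (T1, T3, ..., T17), plus T26 and T52; gait analysis is done five times.

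**Sample size.** Section 4.4: 20 per year × 30/12 years = 50, which reproduces the planned number. With two groups and blocks of 4, I take 25 per arm. The protocol gives no effect size, SD, power or withdrawal rate, so everything below rests on assumed values.

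**Bias, simple form.** Let p be the share withdrawn in an arm and g the amount, in SD, by which withdrawn subjects would score below completers. The full-arm mean is (completers' mean) − p × g, so completers overstate their arm by p × g. The bias in the difference is (p_early − p_late) × g.

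| Loss early / late | g | Size of bias (SD) |
|---|---|---|
| equal, same g | any | 0 |
| 10% / 20% | 0.5 | 0.10 × 0.5 = 0.05 |
| 10% / 20% | 1.0 | 0.10 × 1.0 = 0.10 |
| 10% / 30% | 0.5 | 0.20 × 0.5 = 0.10 |
| 10% / 30% | 1.0 | 0.20 × 1.0 = 0.20 |

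With more loss in the late arm the bias runs against early provision; with more loss in the early arm the sign reverses.

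**Bias, cross-check.** Suppose the share q of each arm least able to tolerate testing is withdrawn, that tolerance has correlation r with the endpoint, and that the true effect is zero. Completers' means then shift by r × φ(z_q)/(1 − q). The multiplier of r is 0.195 at q = 10%, 0.350 at 20% and 0.497 at 30%.

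- 10% versus 20%: (0.195 − 0.350) × r = −0.05, −0.08, −0.11 SD for r = 0.3, 0.5, 0.7.
- 10% versus 30%: (0.195 − 0.497) × r = −0.09, −0.15, −0.21 SD. The nominal 5% type I error becomes about 6%, 8% and 10%.
- Equal loss, or r = 0: no bias.

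**Precision.** Detectable difference at 80% power, two-sided 0.05 (sidedness assumed), two-sample t-test:

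| Loss | n per arm | Detectable effect (SD) |
|---|---|---|
| 0% | 25 | 0.809 |
| 10% | 25 × 0.9 = 22.5 | 0.855 |
| 20% | 25 × 0.8 = 20 | 0.909 |

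The normal approximation, 2.80 × √(2/n), gives 0.79, 0.84 and 0.89.

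**The case against.** Several points on the other side stand.

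- A reader might infer that the rule breaks the randomised comparison. The documents do not support that. Bias needs loss that is related to outcome and that differs between arms in rate or mechanism, and no withdrawal rate is given. Even the worst assumed bias, 0.20 SD, is below one standard error of the difference, √(2/25) = 0.28 SD.
- A reader might infer that endpoints are thrown away. Nothing says that collected data are dropped. Most main endpoints are measured two-weekly to T18, and the Barthel at T1, T9 and T17, so a subject withdrawn at week 12 has already contributed. No primary time point is named that would make T26 or T52 decisive. Only the NEADL depends wholly on those visits.
- The heading of 6.6 might suggest that subjects who stop wearing the AFO are lost. Stopping the AFO is not among the withdrawal grounds in 6.4 or 6.4.1, so this is a mismatch of wording only.
- No section ranks the tests by load, and five main endpoints are physical tests. A lighter schedule could not be expected to recover those.
- Subjects who leave entirely by their own wish would be lost under any rule, so the precision figures are upper limits. Withdrawals before AFO use are to be replaced under 6.5.
- Rest, spreading of tests and the exclusion of disorders that affect test performance (4.3) should make the rule bite less often. The study is also explorative and sized by feasibility.

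None of this answers the central point. The protocol offers no partial follow-up, and subjects willing to continue with the lighter scales are stopped anyway.

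**Conclusion.** The point holds as a defect of data collection. Measurement load, judged by the subject or by a researcher who cannot be blinded, leads to full withdrawal, and main-endpoint data that some subjects could still give are not collected. That reading rests on the text alone.

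The effect on the comparison is a threat of uncertain size, from nil up to about 0.20 SD under the loss rates and gaps assumed above. That the loss is related to outcome is an inference from what the tests consist of, and unequal loss between arms is a plausible conjecture. The loss of precision needs neither condition, but counts only for subjects who would have continued in part. With a planned 50 subjects the change is worth making before recruitment proceeds.

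**What to change.** - **6.4.1:** separate stopping particular measurements from leaving the study, so that excessive load leads first to a reduced measurement schedule.
- **6.6:** for subjects who agree, keep collecting the RMI, FAC, Barthel and NEADL at the remaining scheduled visits, at least T26 and T52, and analyse these subjects in the arm assigned. Align the heading with the text.
- **Records:** document by arm the reason for each withdrawal and whether the subject or the researcher triggered it, so that unequal loss can be seen.

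The subject's right to leave at any time is unchanged. The cost is protocol and consent wording and a short contact at the remaining visits for a few subjects. The physical performance tests may still be missing for them.

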## **6.7 Premature termination of the study**

In case of serious adverse events (see paragraph 7.2) the study can be terminated prematurely. In such circumstances, the accredited METC will be notified and the subjects will be informed as soon as possible.

## **7. SAFETY REPORTING**

### **7.1 Section 10 WMO event**

In accordance to section 10, subsection 1, of the WMO, the investigator will inform the subjects and the reviewing accredited METC if anything occurs, on the basis of which it appears that the disadvantages of participation may be significantly greater than was foreseen in the research proposal. The study will be suspended pending further review by the accredited METC, except insofar as suspension would jeopardise the subjects' health. The investigator will take care that all subjects are kept informed.

### **7.2 Adverse and serious adverse events**

Adverse events are defined as any undesirable experience occurring to a subject during a clinical trial. All adverse events reported spontaneously by the subject or observed by the investigator or his staff will be recorded.

A serious adverse event is any untoward medical occurrence or effect that at any dose results in death;

- is life threatening (at the time of the event);
- requires hospitalisation or prolongation of existing inpatients' hospitalisation;
- results in persistent or significant disability or incapacity;
- is a congenital anomaly or birth defect;
- is a new event of the trial likely to affect the safety of the subjects, such as an unexpected outcome of an adverse reaction, lack of efficacy of an IMP used for the treatment of a life threatening disease, major safety finding from a newly completed animal study, etc.

All SAEs will be reported to the accredited METC that approved the protocol, according to the requirements of that METC.

### **7.3 Follow-up of adverse events**

All adverse events will be followed until they have abated, or until a stable situation has been reached. Depending on the event, follow up may require additional tests or medical procedures as indicated, and/or referral to the general physician or a medical specialist.

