### **7.4 Data Safety Monitoring Board (DSMB)**

No DSMB has been established.

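### Sections 6.6 and 7.3 contradict each other on follow-up of an adverse event that is still open when a subject is withdrawn, so its later course and outcome may be lost

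*Protocol*

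**What the plan says.** Section 7.3 of the protocol sets the rule for adverse events: "All adverse events will be followed until they have abated, or until a stable situation has been reached". Follow-up can therefore end in two ways: the event subsides or it becomes stable. The rule covers every adverse event and makes no exception for withdrawn subjects.

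Section 6.6 sets the rule for withdrawn subjects: "No follow-up will take place after subjects have been withdrawn from the study". It makes no exception for open adverse events. Its heading speaks of withdrawal from treatment, while its text speaks of withdrawal from the study.

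Subjects can reach 6.6 by several routes. They may leave on their own wish (6.4). Section 6.4 adds a medical route: "The investigator can decide to withdraw a subject from the study for urgent medical reasons". Section 6.4.1 adds measurement burden: "Subjects will be withdrawn when either the subject him/herself or the researcher indicates that the load of the measurements is too much".

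Section 7.2 covers recording and reporting: "All adverse events reported spontaneously by the subject or observed by the investigator or his staff will be recorded", and "All SAEs will be reported to the accredited METC that approved the protocol, according to the requirements of that METC". One of its seriousness criteria is that an event "results in persistent or significant disability or incapacity". On oversight, section 7.4 says: "No DSMB has been established".

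**The concern.** A site that withdraws a subject with an open adverse event gets opposite instructions from two sections of the same protocol. The medical route in 6.4 makes this foreseeable, because a subject withdrawn for an urgent medical reason is likely to have an event that has not yet settled.

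What is at stake is the end of the event record. Some seriousness criteria in 7.2, such as lasting disability, a longer hospital stay or death, may be met only some time after onset. A site that stops looking at withdrawal may not learn that an event has become serious, and then cannot report it. With no DSMB, the external safety checks that the protocol describes all run to the ethics committee (METC): serious-event reports (7.2), the section 10 notification (7.1) and the annual report (10.3). Each depends on what the site knows. Section 9.3 says that clear risks and benefits of the two groups cannot be specified in advance, so the outcome of adverse events is information the trial needs.

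**Working it through.** The plan gives no figure to reproduce and no arithmetic applies. The check sets the sections side by side for the possible cases.

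1. **Subject stays in the study with an open adverse event.** Only 7.3 applies. There is no conflict.

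2. **Subject is withdrawn, and every adverse event has already subsided or is stable.** 7.3 is satisfied at withdrawal and 6.6 asks for nothing further. There is no conflict.

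3. **Subject is withdrawn with an adverse event that has neither subsided nor stabilised.** 7.3 requires follow-up to continue and 6.6 says none takes place. Both cannot be met. This can arise by any withdrawal route, and the medical route in 6.4 is the clearest.

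Is case 3 resolved elsewhere in the document?

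- No section limits 6.6 to study measurements, and no section says that 7.3 takes precedence or the reverse.
- The 6.6 heading and text name different things (treatment and study), so the heading does not settle the scope.
- Section 7.2 does not resolve it. It requires recording of what subjects report spontaneously or staff observe, and reporting of serious events. It does not require anyone to seek the outcome of an open event. That duty is in 7.3 alone.

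What would be lost in case 3 if a site applied 6.6?

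| Item | Governing section | Effect of applying 6.6 |
|---|---|---|
| Occurrence of the event before withdrawal | 7.2 | None: recorded |
| Serious event recognised before withdrawal | 7.2 | None: reported to the METC |
| Later course and outcome of an open event | 7.3 | May be lost |
| Event that meets a seriousness criterion only after withdrawal | 7.2, dependent on 7.3 | May not be recognised or reported |

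The exposure is the last two rows, for subjects in case 3 only.

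**The case against.** The strongest reply is that the two sentences were never meant to compete. Section 7.3 is the specific rule for adverse events and stands in the safety chapter. Section 6.6 stands in the methods chapter, shortly after withdrawal for measurement burden. Elsewhere, in the Summary and section 3, the protocol uses the term follow-up for scheduled measurements. On that reading 6.6 ends the study visits only, 7.3 continues, and nothing is lost. This is a plausible account of the intention, and it is why loss of data can be called possible but not certain. It does not remove the conflict, because the text of 6.6 is unqualified and a site has to guess.

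Several stronger readings are tempting, and the documents do not support them:

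- A reader might infer that the outcomes of the most serious events will go unrecorded. That follows only if a site lets 6.6 override 7.3. Section 7.2 also still applies: an event that is life-threatening or needs hospital admission counts as serious when it occurs, and is reportable whatever happens after withdrawal.
- A reader might infer that every medical withdrawal leaves an event open. Section 7.3 accepts stability as an end point, so an event may already be closed. Withdrawal under 6.4 is also at the investigator's discretion, so a serious event need not lead to it.
- A reader might want a count of subjects or of weeks lost. The protocol gives no withdrawal or adverse-event rate. Section 7.3 sets no calendar limit, so the time left until the last visit does not measure the follow-up lost.
- A reader might infer from the lack of blinding (6.2) that the loss would differ between the early and late groups. Nothing in the protocol shows this. Absence of blinding makes it conceivable and no more.

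**Conclusion.** The contradiction is real and can be verified from two sentences. For a subject withdrawn with an adverse event that has neither subsided nor become stable, 6.6 and 7.3 cannot both be followed, and the protocol does not say which governs. The consequence is conditional: if a site applies 6.6, the later course and outcome of such events may be lost, including events that become serious only after withdrawal.

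The size cannot be stated as a number from the documents. It is limited to withdrawn subjects with an open event. No efficacy comparison or estimate changes. The conclusion assumes only that such a withdrawal can occur, which 6.4 provides for. The matter concerns site conduct and safety reporting, which the protocol itself fixes, so an analysis plan would not be expected to settle it. Because it touches safety data and is simple to correct, it should be corrected.

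**What to change.** Reconcile the two sections. Limit the sentence in 6.6 to the scheduled study measurements, and add a cross-reference stating that adverse events ongoing at withdrawal are followed as 7.3 already requires, subject to the subject's consent. Bring the 6.6 heading and text into line, so that it is clear whether withdrawal from treatment or from the study is meant.

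This adds no new safety rule, since it only makes 6.6 consistent with the rule the protocol already has. The cost is about one sentence of protocol text and, in practice, a telephone call or chart check for the few withdrawn subjects who have an open event.

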### **7.4 Data Safety Monitoring Board (DSMB)**

No DSMB has been established.

## **8. STATISTICAL ANALYSIS**

### **8.1 Descriptive statistics**

Descriptive statistical methods are applied for each of the outcome measures. Presentation of data is done by calculation of mean  $\pm$  standard deviation (SD), range and frequency. Furthermore, descriptive statistics are used to describe the subject and treatment characteristics (paragraph 6.1.3).

### **8.2 Univariate analysis**

A significance level of  $\alpha = 0.05$  will be used in data analysis. If necessary, adjustments for multiple comparisons will be applied.

Analysis of this study consists of studying the effects of timing of providing AFOs on the outcome measures. Comparison of the data between the “early” and “late” AFO group will be performed using corresponding parametric/non-parametric tests according to the features of the outcome measures involved (t-test).

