In a longitudinal study the included subjects will be assessed repeatedly during the first year after stroke. In order to measure the effects of timing of providing an AFO, the ICF levels activity and function will be used. On the ICF level “function”, gait analysis, instrumented tests and various clinical tests will be performed. On the level of “activities”, several clinical tests will be assessed (see paragraph 6.1). Furthermore, the incidence of falls and quality of

life after stroke will be assessed using questionnaires. The first measurements will be performed as soon as possible after admission into the Roessingh. Within the first 6 months after stroke, the various measurements will be performed with 2-week/monthly intervals (see paragraph 6.3). Follow-up measurements will be performed 1 year after stroke. The measurements will be performed at the Roessingh Rehabilitation Centre, and in the gait laboratory at the Roessingh Research and Development, Enschede.

Flowchart:

[figure not shown]

T1 = week of inclusion and providing AFO to "early" group;  
T9 = week of providing AFO to "late" group

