### 4.2 Inclusion criteria

- admission into the Roessingh Rehabilitation Centre
- unilateral ischaemic or haemorrhagic hemiparetic stroke (single and first ever or history of previous stroke with full physical recovery)
- time since stroke max 6 weeks
- age 18 years or older
- indication to use an AFO during rehabilitation because of:
  - problems with stability in stance
  - problems with footclearance during swing
  - problems with foot prepositioning in early stance
- no severe deficits in communication
- no severe deficits in memory and understanding

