#### **4.4 Sample size calculation**

To our knowledge this is the first explorative research studying the effects of timing of AFOs in the rehabilitation after stroke. As such, data of earlier experiments with timing of AFOs are not available for power calculation.

The number of subjects that can be included in the study will depend on the number of acute stroke patients admitted to the rehabilitation centre. Based on estimations of therapists and rehabilitation physicians of the Roessingh Rehabilitation Centre and the Annual Reports of the Roessingh, we estimate that approximately 20 subjects can be included each year. The time during which subjects can be included is defined at 30 months (starting from September 2009). Within the available inclusion time of 30 months therefore 50 subjects can be included.

An interim power-analysis will be performed after including 30 subject to estimate whether including 50 subjects will be enough to reach sufficient statistical power. If this interim analysis reveals that more than the planned 50 subjects are needed, an amendment will be applied to include more subjects.

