### **6.1.3 Other study parameters**

At the start of the study the following subject characteristics will be measured:

- sex
- age (years)

- weight (kg)
- height (m)
- time since stroke (weeks)
- affected side (left/right)
- stroke type (ischaemic or haemorrhagic)
- dominant side (left/right)
- proprioception and sensation disorders (Modified Nottingham Sensory Assessment, Lincoln et al. 1998)
- cognition (Mini-Mental State Examination, Folstein et al. 1975)
- communication level (spontane communicatie onderdeel, Utrecht Communicatie Onderzoek, Blauw and Koning, 1988)

The characteristics of the treatment of the individual subject will be measured using questionnaires for clinicians and subjects (see attachment 1):

- use of additional walking aids
- standing and walking
- falling
- medication (spasticity related)
- AFO use

Furthermore, a questionnaire will be used to assess pain of the feet/ankles and using the shoes and AFO (see attachment 2).

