### Gait analysis

Gait analysis will be performed at the RRD. Both groups will be measured five times (see table 1):

- T1: The first measurement will be performed at the end of the first week of the study (T1). Subjects in the “early” AFO group receive their AFO at the beginning of this week and are measured with and without AFO. Subjects in the “late” AFO group will be measured without AFO.
- T9: The second gait analysis will be performed in week 9 of the study (T9). Subjects in the “early” group are now using the AFO for 8 weeks, subjects in the “late” group receive their AFO in this week. From now on both groups will be measured with and without using the AFO.
- T17: The third gait analysis will be performed in week 17 of the study (T17). Subjects in the “early” group are using their AFO for 16 weeks, subjects in the “late” group are using their AFO 8 weeks.
- T26: The fourth gait analysis will be performed in week 26 of the study, approximately 6 months after stroke.
- T52: The last measurement will be performed 1 year after stroke.

Measurements will be performed while walking at comfortable speed. If necessary, subjects can use walking aids (e.g. canes). The movements of the body while walking will be recorded with a VICON video based 3D kinematic measurement system (VICON-MX13+, Vicon Oxford Metrics, Oxford, UK), consisting of 6 infrared cameras, using passive reflexive markers. Subjects are asked to put on a short and top so the skin is suitable for proper marker placement. These markers will be attached to the subject on the feet, lateral malleolus, tibia, knee and femur of both legs, as well as on the pelvis. Vertical ground reaction forces will be measured with force plates, covered in the level walkway (AMTI-OR6-5, Advanced Medical Technologies, Inc, Massachusetts, USA). During the gait analysis muscle activity will be recorded using surface EMG from several superficial muscles of both legs using wet-gel silver/silver-chloride electrodes. Signals will be collected from the m. Rectus Femoris, m. Vastus Lateralis, m. Semitendinosus, m. Gastrocnemius and m. Tibialis Anterior. Electrode placement, skin preparation and related issues are performed according to the guidelines presented by SENIAM (Hermens et al. 1999).

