| T1                                   | Modified Nottingham Sensory Ass
Mini-Mental State Examination
Utrecht Communicatie Onderzoek                                                                                                                                                             | proprioception and sensation
cognition
communication                                                                                                                             | *
**
***                                |
| T1, T9, T17, T26, T52                | Clinical Gait analysis
Mappam test
Modified Ashworth Scale
Brunnstrom Fugl Meyer (leg portion)
Passive ankle range
Barthel Index
Nottingham Extended ADL (T26/52)
Stroke Impact Scale                                                     | joint angles/EMG/GRF
stretch reflex, instrumented
resistance to passive
motion
synergies
passive range of motion
ADL
extended ADL
quality of life after stroke | *
*
*
*
*
**
**
**       |
| T1-T18: 2-week interval,
T26, T52 | Motricity Index (leg portion)
10-m walking test
6-min walking test
Berg Balance Scale
Timed Up and Go test
Stairtest
Rivermead Mobility Index
Functional Ambulation Categories
therapist- and subject questionnaires
(attachment 1) | muscle control and strength
walking speed
walking endurance
balance
mobility
mobility
mobility
independence in walking
treatment and falls                     | *
*
*
*
*
*
**
***
** |
| T1-T26: every month,
T52          | Falls Efficacy Scale
subject questionnaire (attachment 2)                                                                                                                                                                                                   | fear of falling
pain and AFO/shoe use                                                                                                                                               | **
**                                      |

*T1 = week of inclusion and providing AFO to the “early” group;*

*T9 = week of providing AFO to the “late” group;*

*T26 = 6 months after stroke*

*T52 = 12 months after stroke*

*\*) physical test; \*\*) questionnaire; \*\*\*) rating scale*

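### Section 8.2 plans only a two-group test for a longitudinal trial and states no use of the repeated visits, an earlier value or time since stroke, which costs precision

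*Protocol*

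**What the plan says.** Section 8.2 is headed as a univariate analysis. It compares the two groups using "corresponding parametric/non-parametric tests according to the features of the outcome measures involved (t-test", at a significance level of 0.05. It names no visit, no model for repeated measurements and no covariate. Section 8.1 uses the subject characteristics of section 6.1.3, among them time since stroke, for description only.

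The design is richer than this. Section 3 states: "In a longitudinal study the included subjects will be assessed repeatedly during the first year after stroke". Table 1 schedules most of the main mobility tests every two weeks from T1 to T18, then at T26 and T52. Entry is allowed over a range (section 4.2: "time since stroke max 6 weeks"). Randomisation (section 6.2) is in blocks of 4, with no stratification stated.

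The sample size is a feasibility figure (section 4.4: "Within the available inclusion time of 30 months therefore 50 subjects can be included"). A power analysis after 30 subjects may lead to an amendment to include more.

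Two features of section 6.3 limit the remedy. The early group receives the AFO at the beginning of the T1 week, and the clinical tests are said to be done with the AFO. Only the gait analysis is planned both with and without it at T1 in that group.

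On visit timing, the gait analysis text says: "The fourth gait analysis will be performed in week 26 of the study, approximately 6 months after stroke". The Table 1 footnote says: "T26 = 6 months after stroke".

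**The concern.** The protocol justifies the trial by the need to move from cross-over to longitudinal studies, then plans an analysis that names nothing longitudinal. Section 3 says that spontaneous recovery is almost complete at about 6 to 10 weeks, so subjects who enter at different times up to 6 weeks are at different points of that recovery. Function at entry and time since stroke can therefore be expected to carry some prognostic information.

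With about 25 subjects per arm, unexplained variation makes the comparison imprecise, and a chance imbalance in severity or time since stroke stays in the estimate. The choice also affects the interim power analysis. If that rests on an unadjusted test, it may call for more subjects than an adjusted analysis would need.

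**Working it through.** **Inputs.** From the protocol: alpha 0.05 (8.2), about 20 subjects a year for 30 months (4.4), two groups in blocks of 4 (6.2), and the visits in Table 1. Assumed: two-sided testing, 25 per arm, no dropout, and the correlation r between the covariates and the outcome. The protocol gives no SD, correlation, effect size or power.

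**The plan's own figure.** 20 × 30/12 = 50, as stated.

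**Visits.** T1, T3, T5, T7, T9, T11, T13, T15 and T17 are 9. With T26 and T52 there are 11 for most mobility tests. The Barthel Index has 5 (T1, T9, T17, T26, T52) and the Nottingham Extended ADL has 2 (T26, T52).

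**Unadjusted t-test.** The noncentrality is d × √(n/2) with n = 25 and 48 degrees of freedom. The difference detectable with 80% power is 0.81 SD. The normal approximation gives (1.96 + 0.84) × √(2/25) = 0.79. Power for 0.5 SD is 41%.

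**Adjusted comparison at one visit.** The residual variance is (1 − r²) × SD², with one degree of freedom lost for one covariate. The detectable difference is about 0.81 × √(1 − r²), and the equivalent unadjusted total is 50/(1 − r²).

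| Assumed r | Variance removed | Detectable at 80% power | Equivalent subjects | Power for 0.5 SD |
|---|---|---|---|---|
| 0 (unadjusted) | 0% | 0.81 SD | 50 | 41% |
| 0.3 | 9% | 0.77 SD | 55 | 44% |
| 0.5 | 25% | 0.70 SD | 67 | 52% |
| 0.7 | 49% | 0.58 SD | 98 | 68% |

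**Time since stroke alone.** An assumed correlation of 0.1 to 0.3 removes r² = 1% to 9% of the variance.

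**Chance imbalance.** The standard error of a between-arm difference in any baseline factor is √(2/25) = 0.28 SD. A difference of 0.3 SD or more in either direction (0.3/0.28, about 1.06 standard errors) occurs in about 29% of such trials.

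**Repeated visits.** Take the mean of 4 visits after T1, equal correlation r between all visits, and adjustment for a clean pre-treatment value. The variance is (1 + 3r)/4 − r². At r = 0.5 this is 0.625 − 0.25 = 0.375, with 81% power for 0.5 SD. At r = 0.7 it is 0.775 − 0.49 = 0.285, with 90% power. These are upper bounds: they assume a constant effect, which is not expected because the late group receives its AFO at T9, and a pre-treatment value that the present schedule does not secure.

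**Why the T1 clinical tests cannot simply be the covariate.** If the early group's T1 value already contains an immediate AFO effect e, adjusting for it shifts the estimate by −r × e. With r = 0.7 and an assumed e of 0.2 SD, the shift is −0.14 SD, so a true 0.5 SD would be estimated as 0.36 SD.

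**T26.** Taking 6 months as 26 weeks after stroke, a subject entering at week 2 reaches it at about study week 26 − 2 = 24. One entering at week 6 reaches it at about 26 − 6 = 20. The other definition is study week 26 for both.

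**The case against.** An unadjusted comparison of randomised groups is a valid test. The study calls itself explorative, and covariates, covariance structure and missing-data handling are commonly left to a statistical analysis plan, which may exist. The validity point stands: a reader might infer that the planned test is biased, and it is not. The analysis-plan point stands only in part, because 8.2 does not defer the choice but names a univariate two-group test. A longitudinal adjusted model would depart from that text.

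A reader might also infer that raw values will be tested visit by visit, dropping anyone who misses a visit. Section 8.2 does not say so. Change scores or a summary measure would fit its wording, and non-parametric tests are allowed.

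A reader might infer that a large share of the information is wasted. No correlation is given, and at r = 0.3 the gain is small. Nor is the analysis the only source of precision, since section 4.4 lets the number rise by amendment.

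The strongest objection concerns the obvious remedy of adjusting for each outcome's T1 value. For the main tests performed with the AFO, the early group has no T1 value free of it, so this would remove part of the effect. That objection stands and limits the fix.

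On T26, inclusion is in practice within about 14 days of stroke, so the usual gap is about 2 weeks and the 6-week case is the extreme. T52 is consistently 12 months after stroke, so the documents give no ground for re-anchoring it.

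**Conclusion.** The point holds as a mismatch between design and stated analysis, with a cost in precision rather than validity. Section 8.2 states no use of the repeated visits, an earlier value or time since stroke, although all are recorded. With 25 per arm the planned test has 80% power only for about 0.81 SD. Adjustment would bring this to between 0.77 and 0.58 SD for assumed correlations of 0.3 to 0.7.

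Where the true gain falls in that range cannot be settled from the protocol. Time since stroke alone probably adds little beyond correcting chance imbalance. For one visit with complete data, a repeated-measures model gains mainly through its covariates. Its further value is that it uses every visit, keeps subjects with a missed visit and shows how the arm difference changes around T9.

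The two definitions of T26 are a separate and smaller inconsistency.

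**What to change.** In section 8.2:

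- For the continuous main measures, replace the t-test with a linear mixed model for repeated measures with arm, visit and arm-by-visit terms. Use a parsimonious covariance structure: an unstructured one over ten visits after T1 would need 10 × 11/2 = 55 parameters from 50 subjects.
- Adjust for time since stroke and for T1 measures that do not depend on wearing the AFO, for example the leg Motricity Index. Section 6.3 says that all clinical tests are done with the AFO, so state that this measure is taken without it.
- Do not adjust for T1 clinical tests done with the AFO in the early group. Use an outcome's own T1 value only if the T1 clinical tests are scheduled before the AFO is handed over.
- Use an ordinal or rank-based adjusted analysis for the Functional Ambulation Categories.
- Base the interim power analysis at 30 subjects on this model.

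Separately, choose one definition of T26 and use it in both section 6.3 and the Table 1 footnote. Leave T52 as it is.

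The cost is a change of wording and a little more analysis work. Using the outcomes' own T1 values would also change the order of procedures in the T1 week.
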